### Ethics consideration

4.4

The study protocol was approved by Guangzhou Sport University (ID number: 2023LcLL-71).

### Statistical analysis

4.5

In the initial phase of our statistical analysis, we will employ descriptive statistics to summarize the participant characteristics, including demographics, baseline health measures, and other relevant variables. This step will involve calculating means, standard deviations, and proportions to provide a clear overview of the study population. Following this, comparative analyses between the intervention and control groups will be conducted using independent *t*-tests (or Mann–Whitney U tests for non-normally distributed data) for continuous variables, and Chi-square tests (or Fisher’s exact tests) for categorical variables. This will enable us to detect any significant differences arising from the intervention.

Considering the multiple assessment points in our study, longitudinal data analysis techniques will be crucial. These methods, including repeated measures ANOVA or mixed-model ANOVAs, will allow us to track and analyze changes over time both within and between participant groups. This approach is essential for understanding the dynamics of the intervention’s impact, accounting for both individual variations and time-dependent factors.

To quantify the intervention’s effectiveness, we will calculate effect sizes, providing a measure of the practical significance of our findings. The handling of missing data, a common challenge in longitudinal studies, will be addressed through methods like multiple imputation or last observation carried forward, ensuring the robustness of our results. All statistical tests will be two-tailed, with a significance level set at *p* < 0.05. We plan to use sophisticated statistical software such as SPSS or R for these analyses, enabling us to apply the most appropriate and advanced statistical techniques for our data.

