**Methods:**

The study is conducted in two phases. Initially, 1,000 participants will be recruited for AI model training and testing, with 800 forming the training set, augmented by 9,200 simulated samples generated by ChatGPT, and 200 as the testing set. Data annotation will be performed by experienced physicians from the Department of Mental Health at Guangdong Second Provincial General Hospital. Subsequently, a randomized controlled trial (RCT) with 40 participants will be conducted to compare the AI-driven exercise prescriptions against standard care. Assessments will be scheduled at 6, 12, and 18 months to evaluate cognitive, physical, and psychological outcomes.

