### Study design

2.1

In the first phase, we focus on developing a multimodal data-driven intelligent system for exercise prescription. To achieve this, we will initially recruit 1,000 participants for AI model training and testing. Of these, 80% (800 participants) form the training set. To enhance the robustness and generalizability of the AI model, we will use ChatGPT to simulate an additional 9,200 cases based on the initial 800, resulting in a comprehensive training set of 10,000 instances. The remaining 20% (200 participants) will be reserved as a testing set. This diverse dataset will then be annotated by a team of 10 experienced doctors from the Department of Mental Health at Guangdong Second Provincial General Hospital. Their expertise will ensures the accuracy and clinical relevance of the data labeling, which is critical for the development of a reliable and effective AI system.

In our analysis, we will set the effect size at 0.5 to assess the intervention’s effectiveness. This value represents a medium effect size, which is considered substantial in the context of our study. Following the development and preliminary testing of the AI model, the second phase of the study will involves an RCT with 50 participants. These participants are randomly divided into two groups: 25 in the experimental group and 25 in the control group. The experimental group will receives personalized exercise prescriptions generated by the newly developed AI system, while the control group will receives standard exercise recommendations. This phase aims to evaluate the efficacy of the AI-driven exercise prescription system in a real-world clinical setting. The RCT’s design ensures that the results are robust and can be attributed specifically to the intervention, thereby providing strong evidence of the system’s potential benefits for individuals with mental illnesses.

The effectiveness of the AI-driven exercise prescriptions is evaluated at multiple time points: initially at the end of the 6 months trial period (Trial Completion Assessment), followed by a 6 months follow-up assessment and a 12 months follow-up assessment. These assessments are designed to track and compare the short-term and long-term impacts of the AI-driven exercise prescriptions on the mental health outcomes of the participants (shown in Figure 1).

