### RCT design and methods

4.1

Our study employs a parallel-group RCT to evaluate the effectiveness of an AI-based exercise prescription system in mental health management. Participants are divided into two groups: an intervention group and a control group, each consisting of 25 individuals. This balanced design allows for a robust comparison of outcomes between the groups, thereby providing reliable evidence on the impact of the AI-driven intervention. The randomization process involves a computer-generated sequence, ensuring an unbiased assignment of participants into the intervention group (*n* = 25) and the control group (*n* = 25). Stratification is conducted based on key variables such as age, gender, and specific mental health diagnoses to maintain comparable groups. This methodology is critical for mitigating potential confounding factors and ensuring the validity of the study results. In the intervention group, each participant receives a personalized exercise prescription tailored by the AI system, based on their unique health profile. This approach aims to maximize the efficacy of the exercise regimen in improving mental health outcomes. The control group, on the other hand, receives standard care practices, which may include general health advice or standard exercise recommendations. The distinction in treatment between the groups is central to evaluating the added value of the AI-driven exercise prescriptions.

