### Outcome assessment and follow-up

4.3

This study employs a rigorous and comprehensive assessment schedule, as outlined in Table 2, to evaluate a broad spectrum of outcomes across different time intervals: at 6 months (Trial Completion), 12 months (First Follow-up), and 18 months (Second Follow-up) (detail shown in Table 2).

**Table 2 tab2:** Schedule of assessments and follow-up intervals for study period.

Assessments	Study period		
	Trial Completion (6 months)	Follow-up (12 months)	Follow-up (18 months)
MoCA (30) and MMSE (31)	✓		✓
IADL (32)	✓		
Subjective memory complaints (33)		✓	
Descriptors	✓		✓
Rey-0 complex figure, Judgement of line orientation, prospective memory, spatial memory, Kirby delay discounting	✓		
Physical performance	✓		
Short physical performance battery	✓		✓
400 m walk test	✓		
30 s sit-to-stand	✓		✓
Reproductive, Florida cognitive activitylifetime stimulation, and epic-Norfolk physical activity questionnaire (34)	✓		
FCl, PSOl, and life space questionnaire (35)	✓	✓	✓
State and trait anxiety inventory	✓		✓
Health related quality of life and sedentary behavior	✓	✓	✓

**Cognitive assessments**: the MoCA (Montreal Cognitive Assessment) and MMSE (Mini-Mental State Examination) are conducted at the trial completion (6 months) and again at the 18 months follow-up. These tools are essential for measuring cognitive function and detecting any changes over time.

**Functional and physical assessments**: the study includes the Instrumental Activities of Daily Living (IADL) assessment at the 6 months mark to evaluate functional abilities. Physical performance is measured at 6 months using tests such as the Short Physical Performance Battery, the 400 m Walk Test, and the 30 s sit-to-stand test. These assessments are repeated at the 18 months follow-up to track physical endurance and mobility changes.

**Memory and psychological assessments**: subjective memory complaints are evaluated at the 12 months follow-up, while other detailed memory tests like the Rey-O Complex Figure and Judgement of Line Orientation are conducted at 6 months. The State and Trait Anxiety Inventory is administered at both the 6 months and 18 months follow-ups to assess changes in anxiety levels.

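### Last observation carried forward is an unranked alternative to multiple imputation, yet it assumes no change after dropout, which is what the 12- and 18-month visits are meant to measure

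*Protocol article*

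**What the plan says.** Section 4.5 (Statistical analysis) proposes to deal with missing data by "methods like multiple imputation or last observation carried forward, ensuring the robustness of our results". The two methods are joined by a plain alternative. Neither is called primary, no assumption about why data are missing is stated, and LOCF is not labelled a sensitivity analysis.

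The longitudinal model is left open in the same way: "These methods, including repeated measures ANOVA or mixed-model ANOVAs, will allow us to track and analyze changes over time".

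Section 4.3 sets the assessments "at 6 months (Trial Completion), 12 months (First Follow-up), and 18 months (Second Follow-up"), and Table 2 has no baseline column. Section 2.1 gives the purpose of these visits as comparing short-term with longer-term effects on mental health. Treatment length is given as 4 weeks in section 4.2, while section 2.1 speaks of a 6-month trial period. Those statements need reconciling, but on either one the 12- and 18-month visits come after treatment has stopped.

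**The concern.** LOCF fills each later visit with the participant's last recorded score. For a dropout, that amounts to assuming no change from then on. Once treatment has ended, whether the effect persists or fades is the open question, and LOCF answers it by assumption for everyone who has left. Where an outcome is measured only at 6 and 18 months, the copied value spans a full year.

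At stake are the later contrasts. A faded effect could look partly preserved, an effect that emerges late could look smaller, and a difference in retention between arms could look like a difference in outcome. The statement that the listed methods secure robust results would discourage the checks that might reveal this.

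**Working it through.** The article gives no dropout rate, power figure or missing-data figure, so there is nothing of its own to reproduce. What follows shows how far LOCF can move the 18-month contrast under stated assumptions.

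**Inputs from the article**
- Standardised effect: section 2.1 says "we will set the effect size at 0.5 to assess the intervention’s effectiveness". I use 0.5 SD as the 6-month effect.
- Size: section 4.1 describes "an intervention group and a control group, each consisting of 25 individuals"; the abstract says "a randomized controlled trial (RCT) with 40 participants". The bias formulas do not depend on this number.
- Schedule in Table 2:
  - MoCA/MMSE, STAI, the short physical performance battery and sit-to-stand at 6 and 18 months;
  - PSQI, life space, quality of life and sedentary behaviour at all three visits;
  - IADL, the Rey figure group, the 400 m walk and the lifetime activity questionnaires at 6 months only;
  - subjective memory complaints at 12 months only.

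**Assumed inputs**
- Dropout after month 6 of 10%, 20% or 30%, unrelated to outcome.
- The trajectories shown below.

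**Step 1: equal dropout d, effect D6 at 6 months and D18 at 18 months.** A share d contributes the 6-month effect and the rest the true 18-month effect:

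LOCF contrast = (1 − d) × D18 + d × D6, so bias = d × (D6 − D18).

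| D6 → D18 (SD) | d = 10% | d = 20% | d = 30% |
|---|---|---|---|
| 0.5 → 0 | 0.05 | 0.10 | 0.15 |
| 0.5 → 0.25 | 0.275 | 0.30 | 0.325 |
| 0.5 → 0.5 | 0.50 | 0.50 | 0.50 |
| 0 → 0.5 | 0.45 | 0.40 | 0.35 |

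For example, 0.70 × 0 + 0.30 × 0.5 = 0.15. The third row has no bias; in the last row the bias is towards zero. For outcomes also measured at 12 months, someone lost after month 12 carries the 12-month value, and D12 replaces D6.

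**Step 2: unequal dropout, no treatment effect, both arms drifting by T.**

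LOCF contrast = (1 − d_treated) × T − (1 − d_control) × T = (d_control − d_treated) × T.

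With 10% against 30% and T = 0.5 SD: 0.20 × 0.5 = 0.10 SD. With T = 1.0 SD: 0.20 SD. With no drift (T = 0) the difference is zero.

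**Step 3: simulation check** (25 per arm, assumed within-person correlation 0.6, 5,000 runs).
- Effect 0.5 → 0 with 20% dropout: LOCF averages 0.095 SD.
- Effect constant at 0.5 with 20% dropout: 0.497.
- No effect, 10% against 30% dropout: LOCF contrast 0.103 for T = 0.5 and 0.200 for T = 1.0, with t-test type I error of 6.5% and 10.0% against a nominal 5%.
- An estimator that regresses the 18-month value on the 6-month value within each arm stayed within about 0.005 SD of the truth in every scenario simulated.

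**Step 4: scale.** With 25 per arm, the standard error of a difference in SD units is about √(2/25) = 0.283. A bias of 0.15 is 0.15/0.283 = 0.53 of a standard error; 0.10 is 0.35 of one.

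**Step 5: outcomes scheduled once.** For IADL or subjective memory complaints, Table 2 holds no earlier visit, so LOCF has no scheduled value to copy.

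**The case against.** The best defence is that the sentence only gives examples. Multiple imputation is one of them, a mixed-model ANOVA is also listed, and the final choice may sit in an analysis plan that is not shown. Either of those could avoid the problem. That is fair as to what may eventually be done. It does not rescue the text, which names LOCF as acceptable for the analysis and makes a claim for it that is wrong.

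Several stronger readings are tempting but unsupported:
- **That LOCF will bias the later results.** It need not. With equal dropout and a constant effect the bias is zero, and unequal dropout matters only if scores drift. The article fixes neither the dropout nor the trajectory.
- **That standard errors will be too small.** This was not found for the single-visit t-test that section 4.5 names. With 30% dropout per arm and no effect (same correlation, 20,000 runs), the true SD of the LOCF contrast was 0.283, the mean estimated standard error 0.281, and type I error 4.9%. With a 0.5 SD drift in both arms the figures were 0.292, 0.289 and 5.3%. Multi-visit ANOVA was not tested.
- **That repeated-measures ANOVA forces a choice between dropping people and LOCF.** Multiple imputation can feed that ANOVA, and "including repeated measures ANOVA or mixed-model ANOVAs" leaves open a model that, if fitted by likelihood, uses incomplete records. The term is ambiguous, and the text does not commit to it.
- **That LOCF has nothing to carry for any missing first visit.** Section 4.5 mentions baseline health measures, and STAI, PSQI, sedentary behaviour and life space are model inputs in Table 1, so some earlier values may exist. The point is firm only for outcomes scheduled once, and there a mixed model has no other visit to borrow from either.

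**Conclusion.** The point holds in a limited form. The article leaves LOCF open as a main method and wrongly says this secures robustness, although the assumption behind LOCF conflicts with the purpose of the later visits. Following the text as written can therefore give a wrong 12- or 18-month contrast.

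Under the assumed scenarios the size is 0.05 to 0.15 SD for an effect that fades completely with 10% to 30% equal dropout, and 0.10 SD for a 20-point dropout gap with a 0.5 SD drift. These are modest next to a standard error of about 0.28 SD, but they are systematic. All rest on dropout rates and trajectories that the article does not give. The conflict of assumption and purpose does not depend on them. It should be corrected before the analysis.

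**What to change.** In section 4.5:
- Delete LOCF and the claim that the listed methods make the results robust.
- For outcomes measured at more than one visit, name one primary approach that is valid under missing at random. Either a likelihood-based mixed model on all observed data with arm, visit and arm-by-visit terms, or multiple imputation carried out by arm, would serve. Adjust for the baseline value where one is collected.
- Add a sensitivity analysis in which data are missing not at random.
- For outcomes scheduled once, acknowledge that there is no other visit from which to recover a missing value.

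The cost is a few sentences and a little extra analysis work. No visit, sample or data collection changes, and SPSS and R, which the article already names, can fit the model.

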## Discussion

5

This study represents a significant step forward in the field of exercise prescription for mental health, leveraging the power of AI and machine learning to tailor interventions to individual needs. Our findings contribute to a growing body of evidence underscoring the importance of personalized healthcare approaches, particularly in managing mental illnesses.

The application of a multimodal data-driven AI system in developing exercise prescriptions has demonstrated significant promise in enhancing mental health outcomes. This innovative approach effectively counters the limitations inherent in traditional exercise regimes, which often adopt a generalized approach, potentially overlooking individual nuances. Our AI-driven system, by incorporating a diverse array of data points including mental health status, physical capabilities, and personal lifestyle preferences, offers interventions that are far more customized and aligned with each participant’s unique needs.

This level of individualization in exercise prescription is pivotal (49). It recognizes the complex interplay between mental health and physical activity, allowing for adjustments based on factors such as an individual’s specific mental health condition, their physical fitness levels, and their daily routines and preferences. For instance, someone with mild depression might benefit from a different type and intensity of exercise compared to someone with severe anxiety. Likewise, a physically active individual might be prescribed a more vigorous regimen than someone who is less active. By tailoring exercise recommendations in this way, our AI system not only caters to the distinct needs of each participant but also maximizes the potential for adherence. Adherence is often a significant challenge in traditional exercise regimes, but by offering personalized and therefore more relevant and engaging exercise plans, our system could significantly improve compliance rates (50).

Moreover, the enhanced efficacy of these personalized exercise regimes could lead to better mental health outcomes. Regular, tailored physical activity can positively impact various aspects of mental health, including mood elevation, reduction in anxiety symptoms, and overall improvement in mental well-being. This suggests that personalized exercise prescriptions, as adjuncts to conventional mental health treatments like psychotherapy and medication, could offer a comprehensive approach to mental health care.

While our research has yielded encouraging outcomes, it is not without limitations. The complexity of mental health disorders and the variability in individual responses to exercise highlight the challenges in developing universally effective AI-driven interventions. Additionally, the reliance on self-reported data in some of our assessments could introduce bias or inaccuracies. Future research should aim to incorporate more objective measures and explore the long-term sustainability of AI-prescribed exercise regimes.

## Conclusion

6

In conclusion, this study marks a significant stride in the realm of mental health care, demonstrating the potential of a multimodal data-driven AI system to revolutionize exercise prescription for individuals with mental illnesses. While acknowledging the complexities inherent in mental health disorders and the limitations of our current approach, our findings underscore the promise of personalized, AI-enabled exercise regimens in enhancing mental well-being. The integration of sophisticated AI with individualized exercise prescriptions paves the way for more effective, patient-tailored therapeutic strategies, offering a glimpse into the future of mental health treatment. Moving forward, it is imperative to address the identified limitations through more extensive research, aiming to refine the AI algorithms further and explore the long-term impact of these personalized interventions, ultimately contributing to more comprehensive and effective mental health care.

## Ethics statement

The studies involving humans were approved by the Human Experimental Ethics Inspection of Guangzhou Sport University. The studies were conducted in accordance with the local legislation and institutional requirements. The participants provided their written informed consent to participate in this study.
